### Exclusion criteria from the analyses

We aim to quantify treatment effects for typical AGR patients. Therefore, we will exclude participants with rare conditions which are likely to affect the health course beyond the effects which can be reasonably assumed from AGR (e.g. organ transplantation, dialysis, chemotherapy) or participants with extremely high health care costs indicating severe conditions. Prespecified criteria used to exclude AGR participants from our analyses are shown in Table 3. Exclusion criteria for AGR participants also apply to potential controls.

**Table 3 Tab3:** Criteria for the exclusion of AGR participants for study analysis

Exclusion criteria	
- Age <70 or >95 years in the intervention billing period Prior to the intervention billing period: - nursing care >2 - <360 insured days in the four previous billing periods - living in a nursing home - hospital costs without out of pocket spending at the last billing period >33.000 € - hospital costs without out of pocket spending during the four last billing periods ≥44.000 € - ambulatory costs during the last billing period ≥2.200 € - ambulatory costs during the four last billing periods ∑ ≥5.500€ - remedy costs without out of pocket spending during the four previous billing periods ≥2.200 € - costs of aid without out of pocket spending during the four previous billing periods ≥4.000 € - drug costs without out of pocket spending during the four previous billing periods AGR ≥11.000 € - total health care costs without out of pocket spending during the four previous billing periods ≥44.000 € - diagnosed AIDS/HIV in the four previous billing periods - chemotherapy in the four previous billing periods - organ transplantation during the four previous billing periods - dialysis during the four previous billing periods	

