### Eligibility criteria for AGR

Due to selective contracts only patients insured by the AOK Nordost are entitled to receive AGR. The geriatric assessment comprises the activity of daily living scale (Barthel-Index), instrumental activity of daily living, Timed “Up & Go”, Chair-Rising-Test, Tandem Stance, Berg-Balance-Scale, and handgrip strength. Eligibility criteria are:Aged 70 and olderat least two geriatric multimorbidity listed in Table 1
impairment or handicap with functional deficitsat least one of the health conditions listed in Table 2

**Table 1 Tab1:** Geriatric multimorbidity

Criteria	ICD-10 codes
Immobility	M96.8, M62.3, M62.5
cognitive impairment	G30, F00 – F07
incontinence	R32, N39, R15
decubitus ulcer	L89, L97, I83, L98
Malnutrition	R64, E41, E43, E44
Disturbances in fluid and electrolyte balance	E86, E87, R60
Depression and Anxiety	F30 – F33, F40, F41
chronic pain	R52
paraesthesia	R20, G50 – G59, G60 – G64
frailty	R54
severe visual or hearing impairment	H25, H28, H52-H54, H90, H91

**Table 2 Tab2:** Eligibility criteria for participation in AGR

Eligibility criteria	ICD-10 codes
Stroke and other cerebrovascular disorders	I60-I69
Status post fracture	S72.-
Arterial obstructive disease with amputation or other surgery	I70.-
Cox and osteoarthritis with Implantation of an endoprosthesis	M16.-, M17.-
Heart failure	I50.-
Exacerbated chronic obstructive pulmonary disease	J44.0, J44.1
Pneumonia and other respiratory tract infections	J10-J22
Other fractures and injuries	S00-T98
Other arthropathies	M00-M25
Spondylopathies and Discopathies, possibly with laminectomy	M45-M51
Coronary heart disease and other heart diseases with cardiac surgery	I05-I09; I20-I25
Delirium and other organic brain psychosis	F00-F05
Osteoporosis	M80-M81
Secondary Parkinsonsyndrom	G20.9
Symptoms, effecting the nervous system and musculoskeletal system	R29.5, R29.6, R29.8

Patients are not eligible for AGR if the assessment indicates a need for hospital admission, if they are not able to participate due to a poor health status or if they are unable to provide informed consent.

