### Sample size

The intervention group consists of all AGR participants, receiving the AGR in Mecklenburg-Vorpommern during the years 2009–2013. This will comprise approximately 700 patients. Controls will be chosen from a pool of around 250.000 members of the AOK Nordost aged 70 years and older. Approximately 2800 controls will be selected from the pool.

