### Matching and statistical analyses

To balance the distribution of potential confounders among cases and controls we will conduct a propensity score matching using a many-to-one matching [16]. Variables for the estimation of the propensity score will be selected based on their expected importance to predict AGR participation as well as the outcomes of interest.

We will perform a two-step matching process. In the first step, for all patients who received AGR in a determined billing period, we plan to match controls with similar morbidity and cost characteristics during a.) the four billing periods prior to the index period in which the intervention took place, and b.) by additionally including the index period in the matching. This first step allows for the definition of an index period in controls. Using variables during the index billing period is complicated by the fact that no information on the temporal sequence of events within a billing period is available due to legally obliged data protection agreements. However, ignoring the index period may lead to a systematic ignorance of events leading to AGR which might have taken place in the index period. Therefore results from both analysis scenarios (a., b.) will be systematically compared. The first-step will be conducted as an exact match (pre matching) on selected variables listed in Table 6. These variables were selected due to their high expected conceptual importance for the estimation of treatment effects. Should no adequate numbers of controls be found, a more lenient matching may be employed. Controls will be drawn with repetition across billing periods. We plan to match up to 100 controls per case at this stage.

**Table 6 Tab6:** Matching criteria

Matching Criterion	Pre Matching	Propensity Score
Age	x ± 2 years	x
Sex	x	x
Area of residence		x
Days being insured		x
Level of nursing care	x	x
Hospital admission yes/no	x	x
Charlson Comorbidity index (CCI)		x
Days spent in the hospital		x
Hospital costs without out-of-pocket spending	x	x
Ambulatory costs		x
Costs of remedy		x
Costs of medical aid		x
Drug costs without out-of-pocket spending	x	x
Total costs with out-of-pocket spending		x
Main diagnoses before AGR		
*Musculo*-*skeletal*	x ^a^	
Status post fracture or joint replacement		
Cox- or gonarthrosis with endoprothesis		x
Other fractures and injuries		x
Other arthropaties		x
Osteoporosis		x
Spondylopathies and Discopathies, possibly with laminectomy		x
*Infection*		

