Pneumonia and other lung inflammations	x ^a^	x
*Cardio*-*vascular system*		
Heart failure		
Chronic obstructive pulmonary disease (COPD)		x
Arterial obstructive disease with amputation or other surgery	x ^a^	x
Coronary heart diseases with surgery		x
Stroke and other cerebrovascular diseases		x
*Neuro*-*psychiatric*		
Delirium and other organic brain psychosis		x
Secondary Parkinsonsyndrom	x ^a^	x
Symptoms, effecting the nervous system and musculoskeletal system		x
Charlson Comorbidity Index		
Any Malignancy	x	x
Cerebrovascular disease		x
Chronic pulmonary disease		x
Congestive heart failure		x
Metastatic solid tumor	x	
Dementia	x	x
Hemiplegia or paraplegia		x
Mild liver disease		x
Myocardial infarction		x
Renal disease		x
Peripheral vascular disease		x
Geriatric Multimorbidity		
Cognitive deficit		x
Chronic pain		x
Depression, Anxiety		x
Incontinence		x
Severe visual/hearing impairment		x
Paraesthesia		x
Immobility	x	x
Chemotherapy	x	x

^a^At least one diagnosis from each main diagnosis group will be used to match controls. Diagnoses are allowed to differ between cases and controls within the main diagnoses group

Subsequently, propensity scores will be calculated using a logistic regression model using coded morbidity and costs under the scenarios a.) and b.), based on all variables listed in Table 6, taking statistical interactions and nonlinear associations into account. Up to four controls may be assigned to one case without repetition.

Appropriate regression models (e.g. time-event models, mixed models, two-part models) will be applied to study effects on our primary and secondary outcomes. Because treatment might also affect censoring due to mortality, competing risks models (using the Fine-Gray approach) will be applied [17]. Patients dying during the follow-up period will not be excluded from the analyses.

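### No rule requires controls to have the two coded geriatric conditions that AGR entry demands, so people who did not meet that entry rule can serve as comparators

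*Protocol article*

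**What the plan says.** All references are to the Methods of the protocol article.

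- **Entry to AGR** (Eligibility criteria for AGR). Patients must be 70 or older, have two or more conditions from Table 1, have a functional deficit, and have one or more condition from Table 2. Both tables are ICD-10 lists. Insurance is also a condition: "Due to selective contracts only patients insured by the AOK Nordost are entitled to receive AGR".
- **Who may be a control** (Exclusion criteria from the analyses; Sample size). "Exclusion criteria for AGR participants also apply to potential controls". The pool is set by membership and age: "Controls will be chosen from a pool of around 250.000 members of the AOK Nordost aged 70 years and older".
- **First matching step** (Matching and statistical analyses). "The first-step will be conducted as an exact match (pre matching) on selected variables listed in Table 6". For the main diagnoses, footnote a says "At least one diagnosis from each main diagnosis group will be used to match controls", and the individual diagnosis within a group may differ between case and control. A looser match is allowed if too few controls are found; its terms are not given.
- **Second step.** A logistic propensity score on the Table 6 variables, with interactions and nonlinear terms. "Up to four controls may be assigned to one case without repetition".
- **Data** (Study design). ICD-10 diagnoses are among the claims supplied, so Tables 1 and 2 can be applied to controls.

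**The concern.** The section on exclusions sets the aim as the effect for the typical AGR recipient. Each recipient was meant to have at least two Table 1 conditions. A control with none or one of them could not have entered the programme and is not the untreated counterpart of a recipient.

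If such controls carry less geriatric burden than the cases they are matched to, their risk of care-level progression, nursing home admission and fracture could be lower for reasons unrelated to AGR. All three primary outcomes would then be compared against a healthier group. This part of the entry rule is recorded in the claims, so the gap is avoidable, unlike the missing clinical assessment scores.

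**Working it through.** **1. The plan's own figure.** Sample size gives the intervention group as "This will comprise approximately 700 patients" and the comparison group as "Approximately 2800 controls will be selected from the pool". With up to four controls per case, 700 × 4 = 2,800, so the figure reproduces. The pool holds 250,000 / 700 ≈ 357 members per AGR patient before any restriction.

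**2. Entry criteria against control rules.**

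| AGR entry criterion | Does it hold for controls? |
|---|---|
| Age 70 or older | Yes, by definition of the pool and Table 3 |
| AOK Nordost insurance | Yes, by definition of the pool |
| One or more Table 2 condition | Largely, through the group-level pre-match, unless the looser match is used |
| Two or more Table 1 conditions | No rule |
| Functional deficit, fitness to take part, consent | Cannot be applied from claims |

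The group marks in Table 6 are read here as footnote a describes them, because the row layout may have suffered in extraction from the PDF.

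**3. The eleven Table 1 conditions in Table 6.**

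- Exact pre-match: immobility. Dementia is also matched exactly, in the Charlson block, and overlaps with cognitive impairment.
- Propensity score only, in the geriatric block: cognitive deficit, chronic pain, depression/anxiety, incontinence, visual/hearing impairment, paraesthesia (6).
- Not in the geriatric block: decubitus ulcer, malnutrition, fluid/electrolyte disturbance, frailty (4).

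Check: 1 + 6 + 4 = 11.

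**4. Pairs that could qualify a patient.**

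- All pairs: C(11,2) = 55.
- Both conditions in the geriatric block: C(7,2) = 21.
- At least one condition absent from it: 55 − 21 = 34.
- Both absent: C(4,2) = 6.
- Both exactly pre-matched: at most C(2,2) = 1 (immobility with cognitive impairment, and only where the latter is coded as dementia).

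For the 34 pairs, the geriatric block cannot reproduce what qualified the patient. For the other pairs, the score tends to balance the conditions across groups but does not oblige any one control to have two. These are counts of pairs, not shares of patients, because the article gives no prevalences.

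**5. Balance on averages is not a per-person rule (illustration, assumed figures).** Suppose each of the eleven conditions has prevalence p in controls, independently. The share with fewer than two is

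(1 − p)^11 + 11p(1 − p)^10

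- p = 0.20: 0.322
- p = 0.25: 0.197
- p = 0.30: 0.113

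Real conditions cluster, immobility is matched exactly, and the other matching variables also act. The figures show the mechanism and do not estimate the share in this study.

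**The case against.** **Controls are far from unselected.** A reader might infer that controls meet none of the AGR entry criteria. The article does not support that. Age and insurance hold throughout, and the Table 2 condition is largely imposed at group level. A control must also agree with its case on age within two years, sex, care level, hospital admission, hospital costs, drug costs, dementia and immobility. This makes gross mismatch unlikely, but it leaves the Table 1 rule unenforced.

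**The propensity score may do the work.** If people below the threshold cannot receive AGR, a well-specified score with interactions gives them low values, and few would be matched. That is fair as far as it goes. However, four of the conditions are not in the geriatric block, and the score is a single number in which costs or comorbidity can stand in for missing geriatric conditions.

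**Positivity.** A reader might say that the comparison violates positivity by rule. It does not fit here: an effect in the treated needs comparable untreated people for each AGR patient, and ineligible people elsewhere in the pool do not breach that. The issue is comparability of the controls chosen.

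**Eligibility was settled at the centre's assessment, not from claims.** Some AGR patients may lack the codes beforehand, and the article itself notes that events leading to AGR may fall in the index period. This stands. It argues against dropping uncoded AGR patients from the main analysis, but not against using the codes in matching.

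**The Discussion already concedes residual confounding.** That passage concerns clinical measurements and motivation, which claims do not hold. Table 1 is ICD-coded. Nor is this a detail left to a fuller document: the article sets out the control rules and the matching variables.

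**Conclusion.** The point holds for Table 1. As written, the plan lets people with fewer than two coded Table 1 conditions serve as controls. Table 6 does not close the gap: at most one of 55 qualifying pairs is fully covered by exact matching, and 34 include a condition absent from the geriatric block.

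The consequence is possible bias in the three primary outcomes. A direction against AGR is plausible if under-threshold controls are healthier after matching, but the article does not show it. It would also be wrong to read the 11% to 32% illustration as the expected share of ineligible controls, since it rests on assumed, independent prevalences. The true share cannot be computed from the document. The conclusion assumes that footnote a works at group level as stated and that the looser match is not used; if it is, the Table 2 cover weakens too.

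**What to change.** 1. Build a coded count of Table 1 groups from all eleven conditions, for cases and potential controls alike. Use the four prior billing periods in scenario a, and add the index period in scenario b.
2. Add a yes/no variable for two or more Table 1 groups to the exact pre-matching variables in Table 6. Each control then has the same coded eligibility status as its case, and all AGR patients stay in the main analysis.
3. Report how many AGR patients lack the codes, under each scenario.
4. Add a sensitivity analysis restricted to cases and controls who both meet the coded Table 1 and Table 2 criteria.

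The cost is one derived variable from data already held, one extra analysis, and a somewhat smaller set of possible matches from the roughly 250,000 members. How many remain after pre-matching cannot be shown from the article and should be reported.

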### Outcome measures and data collection

Claims data will comprise the billing periods from 01.01.2008 until 31.12.2014, thus ensuring a minimal observation period of 12 months prior and after the index billing period. All variables are provided for each billing period during the observation period.

The primary outcomes are ‘*progression of nursing care level*’, ‘*admission to nursing home*’ and ‘*incident fractures*’.

Four nursing care levels (0–3) are defined by the German social code XI (SGB XI). The nursing care level needs to be approved by the Medical Review Board of the statutory health insurances (MDK) in a standardised procedure. The definition for nursing care level is described in Table 4 [13]. Elderly who do not reach the requirements for nursing care level I, but need help for daily living (SGB XI § 45a) receive care for their needs. This is referred to as nursing care level 0 [13].

**Table 4 Tab4:** Definitions of the nursing care levels [13]

	Requirements	
Nursing care level	total daily help (including help in household)	personal help (included in total daily help)
1	minimum 1,5 h	>45 min
2	minimum 3 h	≥2 h, 3 times a day
3	minimum 5 h	≥4 h permanent help

The outcomes ‘*admission to nursing home*’ and ‘*incident fractures*’ are both coded as binary variables, stating whether the patients experienced the event after the index billing period or not.

Secondary outcome variables are ‘any *hospital admission*’ (yes/no), ‘*days spent in the hospital*’, ‘*ambulatory care sensitive hospital admissions*’ (yes/no) and ‘*total health care costs from the statutory health insurance perspective*’ during the entire follow-up period and during each billing period in the follow-up period. Ambulatory care sensitive hospital admissions are defined as potentially preventable hospital admissions by interventions in primary care and are displayed in Table 5. Conditions were chosen from two studies [14, 15].

**Table 5 Tab5:** Ambulatory care sensitive conditions used to define hospital admissions to be prevented by AGR (according to [14, 15])

Ambulatory care sensitive conditions	ICD-10 code
Ischaemic heart diseases	I25.0, I25.1, I25.5, I25.6, I25.8, I25.9
Heart failure	I50
Other diseases of the circulatory system	I05, I06, I08.0, I49.8, I49.9, I67.2, I67.4, I70, I73, I78, I80.0, I80.80, I83, I86, I87, I95, R00.0, R00.2
Bronchitis & COPD	J20, J21, J40-J44, J47
Mental and behavioural disorders due to use of alcohol or opioids	F10, F11

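### Time zero is misaligned: AGR patients pass a survival-and-fitness filter around the index quarter that controls do not, so follow-up can start from unequal risk sets

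*Protocol article*

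**What the plan says.** Under Exclusion criteria from the analyses, the article extends Table 3 to the comparison group: "Exclusion criteria for AGR participants also apply to potential controls". The table opens with "Age <70 or >95 years in the intervention billing period Prior to the intervention billing period: - nursing care >2". Age is therefore judged in the index quarter and everything after it looks backwards. That includes "living in a nursing home" and "<360 insured days in the four previous billing periods", the only two criteria that bear on residence and on continued enrolment.

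Under Eligibility criteria for AGR, treated patients meet a further test: "Patients are not eligible for AGR if the assessment indicates a need for hospital admission", nor "if they are not able to participate due to a poor health status or if they are unable to provide informed consent". The description of the intervention gives a usual course of 20 treatment days, and Study design calls it 4 weeks. The index quarter is the one that contains most of those days.

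Controls get their index quarter from the pre-matching: "This first step allows for the definition of an index period in controls". This step is run in two ways: (a) on the four earlier quarters only, and (b) with the index quarter added. The results are to be compared.

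Under Outcome measures and data collection, nursing-home admission and fractures "are both coded as binary variables, stating whether the patients experienced the event after the index billing period or not". The closing paragraph of the statistical section keeps patients who die during follow-up in the analysis. It does not mention deaths in the index quarter.

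**The concern.** Applying Table 3 to both groups looks like equal treatment, but it equalises them only up to the start of the index quarter, while outcome counting starts at its end. In the three months between, an AGR patient has been assessed as able to take part and has attended treatment. A control has only been assigned that quarter.

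Nursing-home admission, a primary outcome, is the most exposed. A control who enters a home in the index quarter has already had the event when counting starts. Depending on how the variable is built, that person is seen as a resident in follow-up and counted as an event, or is coded as having no event although no longer at risk. A control who died in that quarter would be coded as no event under the binary definition, and would add zero hospital days and costs if kept in. The comparison could thus show a difference under no true effect, with a sign set by a coding decision.

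**Working it through.** **The plan's own figures.** 700 AGR patients × 4 controls = 2,800 controls, as stated under Sample size. 4 + 1 + 8 = 13 billing periods, as stated under Study design. Both reproduce. The article states no event rates, so there is no figure for the bias to reproduce.

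**Requirements around the index quarter, side by side**

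| Condition | AGR patients | Controls, scenario (a) | Controls, scenario (b) |
|---|---|---|---|
| Age 70-95 | Table 3 | Table 3 | Table 3 |
| Alive and insured | Implied on the treatment days | No rule | Insured days in the propensity score only |
| Not in a nursing home | No explicit rule; must be able to attend | No rule | No variable in Table 6 |
| No need for admission, fit, able to consent | Required at assessment | No rule | Indirect, through care level, admission and costs |

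**Illustration under no true effect.** Assumed inputs, not from the documents: quarterly risk of nursing-home entry h = 1-3%; quarterly risk of death d = 1.5-4%; constant over 8 follow-up quarters; AGR patients have no index-quarter events and controls carry a full quarter of risk.

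- Risk over follow-up for a person at risk when it starts: F = h × [1 − (1 − h − d)^8] / (h + d)
- AGR patients: F
- Controls, index-quarter entries carried into follow-up: h + (1 − h − d) × F
- Controls, index-quarter entries and deaths coded as no event: (1 − h − d) × F

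Middle case, h = 0.02 and d = 0.025: 0.955^8 = 0.692, so F = 0.02 × 0.308 / 0.045 = 0.137.

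- Carried in: 0.02 + 0.955 × 0.137 = 0.151; risk ratio (AGR/control) 0.137 / 0.151 = 0.91
- Coded as no event: 0.955 × 0.137 = 0.131; risk ratio 1 / 0.955 = 1.05

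| h | d | F | Ratio, carried in | Ratio, coded as no event |
|---|---|---|---|---|
| 0.01 | 0.015 | 0.073 | 0.90 | 1 / 0.975 = 1.03 |
| 0.02 | 0.025 | 0.137 | 0.91 | 1 / 0.955 = 1.05 |
| 0.03 | 0.04 | 0.189 | 0.92 | 1 / 0.93 = 1.08 |

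In numbers, 1-3% of 2,800 is 28-84 controls already admitted, and 1.5-4% is 42-112 already dead, before follow-up starts.

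**How far the assumption about AGR patients matters.** If AGR patients carried the same index-quarter risks as controls, both would be handled alike and the ratio would be 1.00. At given rates, with the AGR patients' risk somewhere between zero and the controls' risk, the distortion lies between 1.00 and the tabulated value.

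**Other assumed rates.** Take a two-year nursing-home risk q of 10-20% and, for controls only, index-quarter death of 1-3% and entry of 0.5-2%.

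- Coded as no event: 1 / (1 − d − h) runs from 1 / 0.985 = 1.015 to 1 / 0.95 = 1.053.
- Carried in: q / [(1 − d − h) × q + h] runs from 0.10 / 0.117 = 0.855 to 0.20 / 0.198 = 1.010.

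Separately, if scenario (a) controls have an excess s of 5-20 percentage points in index-quarter hospitalisation, which raises later risk r = 1.5- to 2.0-fold, the null ratio 1 / [1 + s × (r − 1)] runs from 0.976 to 0.833.

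**The case against.** Several points on the other side stand.

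- **The label.** A reader might infer immortal-time bias. The article does not support this: outcomes count from after the index quarter in both groups, so guaranteed survival in that quarter is not credited to AGR follow-up. Misaligned time zero with healthy-participant selection is the accurate description. A little immortal time could arise only where the four weeks run over into the next quarter.
- **AGR patients are not event-free all quarter.** Treatment takes about four weeks of three months. They can fracture or be hospitalised before or after it, and can die or enter a nursing home afterwards. Nor does AGR by definition mean living at home: eligibility lists no such criterion, and Table 3 has to exclude participants who live in a nursing home. The zero-risk assumption for cases therefore overstates the contrast.
- **The authors saw the index-quarter problem.** They explain that the order of events within a quarter is unavailable and plan scenario (b). It matches on index-quarter care level, admission, and hospital and drug costs, with insured days in the propensity score. A control who dies or leaves in that quarter becomes a less likely match. This narrows the gap. It does not close it: nursing-home status and survival are not in Table 6, and comparing (a) with (b) does not make either one right.
- **Deaths depend on the model.** In a time-to-event or Fine-Gray analysis, a control who died before follow-up has no time at risk. The distortion from deaths needs the binary outcome with such people kept in the denominator. The article states that binary coding and does not exclude them.
- **A condensed article may leave extraction details elsewhere.** That is fair for many details. Here, however, the article does set the eligibility windows and the start of outcome counting, and as written they do not meet.

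**Conclusion.** The point holds as a misaligned start of follow-up. It is most serious under scenario (a) and for nursing-home admission, and is reduced but not removed under (b). At the assumed quarterly risks, a null effect would appear as a nursing-home risk ratio of about 0.90-0.92 or 1.03-1.08, depending on how index-quarter entries are coded. These are upper illustrations for those rates because cases are given no index-quarter risk; other plausible rates give somewhat different values, as shown. None of the rates comes from the documents.

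A reader might infer that the plan is biased in favour of AGR, or by a known amount on every outcome. Neither follows. The direction turns on coding that the article does not fix, and only nursing-home admission has been worked through with these entry and death rates. Fractures, care level, hospital days and costs share the mechanism, but their distortion is not established here.

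**What to change.** Make the end of the index billing period a common landmark. In both scenarios, and before the propensity step, require AGR patients and controls alike to be alive, insured and not in a nursing home at that point. Start the risk period for all outcomes in the next quarter. Report how many in each group the rule removes.

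The article says that all variables are provided for each billing period, so this is a filter on data already held. From a pool of about 250,000 the loss of controls is minor, and a few of the roughly 700 AGR patients would go. With both groups restricted alike, the two sources worked through above (index-quarter deaths and nursing-home entries) disappear and their null ratio returns to 1.00.

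The price is interpretive. Results become conditional on reaching the end of the index quarter outside a nursing home, which is a post-treatment condition for AGR patients, so the counts removed need to be shown by group. Differences in unmeasured fitness also remain. The Discussion partly concedes these by noting that geriatric assessment data are unavailable for controls.
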